### Sample Size

The incidence of major postoperative complications in a recent study with a similar definition was 56.5% (12). Considering this incidence rate, the variables used in sample size calculation are a ratio of sample sizes in negative/positive groups of 1, an area under the receiver-operating characteristics (ROC) curve of 0.7, a type I error probability (α) of 0.05, a type II error probability (β) of 0.1, and a null hypothesis value of 0.5. By using the MedCalc Statistical Software (Ver. 15.8, MedCalc Software Ltd., Ostend, Belgium), we calculated that 41 patients must be enrolled in each group (i.e., with or without major postoperative complications). The sample size extends to 102 patients to anticipate a drop-out rate of 20% due to missing values.

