The above-mentioned CO_2_-derived parameters are increasingly used to identify either low-flow status (PCO_2_ gap) or anaerobic metabolism (Cv-aCO_2_/Ca-vO_2_ and Pv-aCO_2_/Ca-vO_2_) in shock resuscitation, particularly in septic shock (21, 22). However, they are not extensively investigated in cardiac surgery patients. Most studies focused on the predictive value of the PCO_2_ gap (23–26). Some other studies took the Pv-aCO_2_/Ca-vO_2_ into account as well (12, 27, 28). However, Cv-aCO_2_/Ca-vO_2_ was not measured in those studies. This study aims to compare the performance of lactate and CO_2_-derived parameters (i.e., PCO_2_ gap, Pv-aCO_2_/Ca-vO_2_, and Cv-aCO_2_/Ca-vO_2_) in predicting major postoperative complications after cardiac surgery with cardiopulmonary bypass.

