### Statistical Analysis

EpiData (ver. 3.1, Denmark) will be used for data entry and data quality control. Multiple imputations will be used to handle missing data. Perioperative characteristics will be compared according to the occurrence or not of major postoperative complications. Continuous variables will be assessed for normal distribution and presented as means and standard deviations or medians and inter-quartile ranges as appropriate; the inter-group comparison will be performed by using Student's *t*-test for normally distributed variables or Mann-Whitney *U*-test for non-normally distributed variables. Categorical variables will be presented as numbers and percentages and analyzed by using χ^2^-test or Fisher's exact tests as appropriate. Ordinal variables will be analyzed by using the rank-sum test.

ROC curve analysis will be carried out to assess the predictive performance of lactate and CO_2_-derived parameters. The optimal thresholds for predicting major postoperative complications will be determined by maximizing the Youden index. Sensitivity, specificity, predictive values, and likelihood ratios will be calculated. The performance of the ROC curves will be compared by using DeLong's method (41). A *p* < 0.05 (two-tailed) will be considered significant. Analyses will be performed by using SPSS Statistical Software (Ver. 23.0, IBM Co., NY, USA) and MedCalc Statistical Software (for the comparison of ROC curves).

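### Power is given only for one marker's AUC against 0.5; the planned comparison of correlated AUCs, which is the study's aim, has no sample-size justification

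*Protocol article*

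**What the plan says.** The Background section gives the purpose as comparative: "This study aims to compare the performance of lactate and CO_2_-derived parameters", the latter being the PCO2 gap and the two ratios. The Abstract says the same. Under Statistical Analysis, each marker gets its own ROC analysis with a threshold and accuracy measures. DeLong's method, at a two-tailed 0.05 level, is then named for the comparison, in the sentence that begins "The performance of the ROC curves will be compared by using". The Discussion presents the direct comparison of the two respiratory-quotient surrogates as a strength of the study.

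The Sample Size section starts from an expected complication rate of 56.5%. It posits "an area under the receiver-operating characteristics (ROC) curve of 0.7" for a marker. It takes equal numbers of patients in the two outcome groups and sets α at 5%. The remaining inputs are "a type II error probability (β) of 0.1, and a null hypothesis value of 0.5". The result is 41 patients with and 41 without complications, raised to 102 in total for 20% loss to missing values. The section gives no difference between two AUCs, no correlation between markers and no power for the comparison.

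**The concern.** A null value of 0.5 belongs to the question of whether one marker discriminates at all. The question the study is built around is whether one marker discriminates better than another. The signal there is a difference between two AUCs. It is likely to be much smaller than the 0.20 gap between 0.7 and 0.5, and its standard error depends on how strongly the two estimates correlate. The sample size is therefore justified for a different hypothesis from the one in the aim.

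What is at stake is interpretation. If a DeLong test is not significant, the only power figure in the document is 90%. A reader could take the result as evidence that lactate and the CO2-derived parameters perform alike, or that the two respiratory-quotient surrogates are interchangeable, when the study may have had little chance of showing a difference of moderate size.

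**Working it through.** **1. Reproducing the stated sample size.** Inputs from the Sample Size section: AUC 0.70 against 0.50, α 0.05 (two-sided, as under Statistical Analysis), β 0.1, ratio 1. The Hanley-McNeil variance for an AUC of A uses Q1 = A/(2−A) and Q2 = 2A²/(1+A). In large samples with n per group it is (Q1 + Q2 − 2A²)/n.

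- A = 0.5: 0.3333 + 0.3333 − 0.5 = 0.1667.
- A = 0.7: 0.5385 + 0.5765 − 0.98 = 0.1349.
- n = (1.96·√0.1667 + 1.2816·√0.1349)²/0.20² = (0.800 + 0.471)²/0.04 = 40.4, so 41 per group.

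The full finite-sample variance also gives 41 as the smallest n, with power 90.1%. At a 46/36 split, power is 90.0%. For drop-out, 82/0.8 = 102.5, against 102 stated; the rounding is immaterial. The calculation is correct for the hypothesis it names.

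**2. Inputs for the paired comparison.** From the document: 82 evaluable patients and 56.5% incidence, so 0.565 × 82 = 46.3, a 46/36 split. If all 102 are analysable, 0.565 × 102 = 57.6, a 58/44 split. Assumed, because the document gives neither: the AUC pair, and the correlation r between the two AUC estimates, varied from 0.3 to 0.9.

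**3. Formula.** SE(difference) = √(s₁² + s₂² − 2·r·s₁·s₂), with s₁ and s₂ the Hanley-McNeil standard errors. Power = Φ(d/SE − 1.96), where d is the AUC difference.

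Example with 46/36 and AUCs of 0.70 and 0.80: s₁ = 0.0572 and s₂ = 0.0482. At r = 0.5, SE = √(0.003272 + 0.002323 − 0.002757) = 0.0533. Then 0.10/0.0533 = 1.88, and Φ(1.88 − 1.96) = 47%.

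**4. Results.**

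| Assumed AUCs, patients | r = 0.3 | 0.5 | 0.7 | 0.8 | 0.9 |
|---|---|---|---|---|---|
| 0.70 vs 0.80, 82 (46/36) | 36% | 47% | 67% | 83% | 98% |
| 0.70 vs 0.80, 102 (58/44) | 43% | 56% | 77% | 90% | 99% |
| 0.70 vs 0.75, 82 (46/36) | 12% | 15% | 21% | 30% | 52% |
| 0.70 vs 0.85, 82 (46/36) | 71% | 83% | 96% | 99% | >99% |

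Difference detectable with 90% power, reference AUC 0.70:

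| Patients | r = 0.3 | 0.5 | 0.7 | 0.8 | 0.9 |
|---|---|---|---|---|---|
| 82 (46/36) | 0.19 | 0.165 | 0.13 | 0.11 | 0.08 |
| 102 (58/44) | 0.17 | 0.15 | 0.12 | 0.10 | 0.07 |

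A lower pair of AUCs gives less power for the same difference: 0.60 vs 0.70 with 46/36 gives 29%, 38% and 57% at r = 0.3, 0.5 and 0.7. For 90% power at 0.70 vs 0.80, about 173, 125 or 77 patients per group would be needed at those three correlations.

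**5. Check by simulation.** DeLong tests on simulated binormal data with 41/41 patients gave about 34%, 42% and 58% power for 0.70 vs 0.80, at AUC correlations of about 0.26, 0.45 and 0.64. This agrees with the formula. No adjustment for several markers or time points is included; any would lower these figures.

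**The case against.** Four points can fairly be made for the plan.

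- **The protocol does not claim 90% power for the comparison.** A reader might infer that it does, since comparison is the aim and 90% is the only power given. But β is tied openly to a null value of 0.5, and single-marker ROC assessment is itself a planned analysis. This stands: the power statement is not false, but it covers only part of what is planned.
- **Low power is not certain.** The AUC pair and r are assumptions. The two respiratory-quotient surrogates share a denominator, and the Background calls the relation between their numerators almost linear, so a high correlation is conceivable; power for a 0.10 difference then reaches 83-98%. This stands, and the range must run to r = 0.9. It helps less than it seems. The Discussion says it is unclear whether the two are interchangeable, and markers that close may well differ by less than 0.10; for 0.05 at r = 0.9, power is only 52%.
- **82 patients is the cautious case.** The 20% allowance is for missing values, and multiple imputation is planned. With all 102, power for a 0.10 difference is still 43-77% at r = 0.3-0.7. Imputation does not restore full information, so the truth lies between the two cases.
- **Misreading is a risk, not a stated plan.** Nothing in the document says that a non-significant test will be taken as equivalence. Nor can one infer that the comparison will probably be non-significant whatever the true difference: at r = 0.7 a 0.10 difference is detected 67% of the time, and a 0.15 difference 71-96% of the time over r = 0.3-0.7.

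A separate analysis plan could hold the reporting details. It does not explain the mismatch, because the article gives the sample-size calculation in full and its hypothesis differs from the aim.

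**Conclusion.** The point holds and should be fixed. The sample size is correctly computed for one AUC of 0.70 against 0.50 and is not justified for the comparison of correlated AUCs that the study is meant to make. Over r = 0.3-0.7, power for an assumed 0.10 difference is well below 90% with either 82 or 102 patients. It reaches 90% only at high correlation: about 0.8 if all 102 are analysable, and between 0.8 and 0.9 with 82. For a 0.05 difference it stays below 90% throughout the range examined with 82 patients. These figures rest on an assumed reference AUC of 0.70, the assumed r, the stated 56.5% incidence and no multiplicity adjustment. That the 90% does not carry over to the comparison depends on none of these assumptions.

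**What to change.** - **Sample Size section:** state that the 90% power applies only to the test of a single AUC of 0.70 against 0.50. Add the AUC difference detectable with 90% power in the paired comparison, labelled with its assumptions (reference AUC, correlation, number evaluable). The second table under the check supplies the values: about 0.19 down to 0.08 with 82 evaluable and 0.17 down to 0.07 with 102, for r from 0.3 to 0.9.
- **Statistical Analysis section:** report each paired AUC difference with its 95% confidence interval beside the DeLong p-value, and state that a non-significant test will not be read as equal performance.

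The cost is wording and a less favourable stated power. No extra patients are needed. The Trial Status section says that recruitment has not started, so the change can precede any data.

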### Statistical Analysis

EpiData (ver. 3.1, Denmark) will be used for data entry and data quality control. Multiple imputations will be used to handle missing data. Perioperative characteristics will be compared according to the occurrence or not of major postoperative complications. Continuous variables will be assessed for normal distribution and presented as means and standard deviations or medians and inter-quartile ranges as appropriate; the inter-group comparison will be performed by using Student's *t*-test for normally distributed variables or Mann-Whitney *U*-test for non-normally distributed variables. Categorical variables will be presented as numbers and percentages and analyzed by using χ^2^-test or Fisher's exact tests as appropriate. Ordinal variables will be analyzed by using the rank-sum test.

ROC curve analysis will be carried out to assess the predictive performance of lactate and CO_2_-derived parameters. The optimal thresholds for predicting major postoperative complications will be determined by maximizing the Youden index. Sensitivity, specificity, predictive values, and likelihood ratios will be calculated. The performance of the ROC curves will be compared by using DeLong's method (41). A *p* < 0.05 (two-tailed) will be considered significant. Analyses will be performed by using SPSS Statistical Software (Ver. 23.0, IBM Co., NY, USA) and MedCalc Statistical Software (for the comparison of ROC curves).

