## Methods

### Study Design Overview

The present study is a prospective, single-center, diagnostic accuracy study involving patients undergoing elective cardiac surgery. The study will be conducted in Fujian Provincial Hospital, a tertiary hospital and a teaching hospital of Fujian Medical University.

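### Youden-index cut-offs are chosen and evaluated in the same single cohort, so the reported sensitivity, specificity and derived measures will be too favourable; the AUC comparison is not affected

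*Protocol article*

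**What the plan says.** The Statistical Analysis section fixes the threshold rule: "The optimal thresholds for predicting major postoperative complications will be determined by maximizing the Youden index". The next sentence adds: "Sensitivity, specificity, predictive values, and likelihood ratios will be calculated". Markers are then compared by their ROC curves, using DeLong's method.

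The Study Design Overview describes one cohort: "The present study is a prospective, single-center, diagnostic accuracy study involving patients undergoing elective cardiac surgery". Under Sample Size the calculation rests on "an area under the receiver-operating characteristics (ROC) curve of 0.7" against "a null hypothesis value of 0.5" and gives 41 patients per outcome group, raised to 102 in total for 20% drop-out through missing values. The Statistical Analysis section also plans multiple imputation, so the number analysed could lie anywhere from about 82 to 102.

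The article mentions no pre-specified cut-off, split sample, cross-validation, resampling correction or second cohort. The Discussion lists three limitations, and optimism from threshold selection is not one of them.

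**The concern.** The Youden cut-off is the point at which sensitivity plus specificity is largest in the observed sample. Part of that maximum is signal and part is chance. When the same patients supply the accuracy estimate, the chance part is counted as accuracy, so the estimate is biased upward by construction.

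Cut-offs, predictive values and likelihood ratios are the results a clinician is most likely to carry to the bedside. On average they would perform less well in new patients than reported, and a marker with no information would still show a positive J.

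**Working it through.** **1. Reproduce the plan's figure.** Inputs from Sample Size are AUC 0.7 against 0.5, alpha 0.05, beta 0.1 and ratio 1. The two-sided test comes from Statistical Analysis ("A *p* < 0.05 (two-tailed) will be considered significant"). The Hanley-McNeil variance with n per group is

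Var(A) = [A(1−A) + (n−1)(Q₁−A²) + (n−1)(Q₂−A²)] / n², with Q₁ = A/(2−A) and Q₂ = 2A²/(1+A).

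At n = 41:
- A = 0.5: Var = (0.25 + 40 × 0.0833 × 2)/1681 = 0.00411, SE = 0.0641.
- A = 0.7: Var = (0.21 + 40 × 0.0485 + 40 × 0.0865)/1681 = 0.00334, SE = 0.0578.
- 1.960 × 0.0641 + 1.282 × 0.0578 = 0.1997, just under the required 0.20. At n = 40 the sum is 0.2023, which is too large.

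So 41 per group is reproduced (a one-sided test would give 34). For drop-out, 82/0.80 = 102.5, against the stated 102.

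**2. Group sizes.** At the 56.5% incidence given under Sample Size, 0.565 × 82 ≈ 46 (46/36) and 0.565 × 102 ≈ 58 (58/44). Equal splits are 41/41 and 51/51.

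**3. Model (an assumption, not in the article).** The marker is N(μ, 1) with complications and N(0, 1) without, where μ = √2 × Φ⁻¹(AUC). At AUC 0.7, μ = 1.414 × 0.524 = 0.742. In each of 4,000 to 5,000 simulated trials per setting, the cut-off ĉ maximises the sample J = sensitivity + specificity − 1. The true J of that cut-off is Φ(ĉ) − Φ(ĉ − μ). Optimism is the apparent J minus the true J at the same ĉ.

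**4. Mean optimism in J.**

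| With/without complications | AUC 0.5 | AUC 0.6 | AUC 0.7 | AUC 0.8 |
|---|---|---|---|---|
| 41/41 | 0.126 | 0.118 | 0.103 | 0.089 |
| 46/36 | 0.129 | 0.120 | 0.106 | 0.088 |
| 51/51 | 0.114 | 0.104 | 0.091 | 0.079 |
| 58/44 | 0.117 | 0.107 | 0.092 | 0.081 |

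At AUC 0.7 the apparent and true J are 0.372 and 0.267 with 46/36, and 0.361 and 0.269 with 58/44.

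**5. Per measure, with the number of events drawn at 56.5%.**
- 82 patients, AUC 0.7: apparent sensitivity/specificity 0.680/0.692, true 0.629/0.638, so 5.1 and 5.4 points too high.
- 102 patients, AUC 0.7: 0.679/0.683 against 0.633/0.636, so 4.6 and 4.7 points.
- 82 patients, AUC 0.5: 0.558/0.572 against 0.495/0.505, so 6.3 and 6.7 points.

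**6. Derived measures, from the average pair at 82 patients and AUC 0.7.**
- LR+ = 0.680/0.308 = 2.2 apparent, 0.629/0.362 = 1.7 true.
- LR− = 0.320/0.692 = 0.46 apparent, 0.371/0.638 = 0.58 true.
- PPV at 56.5% = 0.384/(0.384 + 0.435 × 0.308) = 0.74 apparent, 0.355/(0.355 + 0.435 × 0.362) = 0.69 true.

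**7. Sensitivity to the model.** With standard deviation 1.5 or 2 in the complication group, or a coarsely rounded marker, optimism is about 0.06 to 0.10. Measured against the best achievable J (0.289 at AUC 0.7) instead of the true J of the chosen cut-off, the excess at 46/36 is 0.372 − 0.289 = 0.083. The bias was upward in every setting tried.

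**8. Does the bootstrap remove it?** In 300 simulated trials at 41/41 and AUC 0.7, the correction moved mean J from 0.373 to 0.303, against a true 0.266. The share removed is (0.373 − 0.303)/(0.373 − 0.266) = 0.070/0.107, about two-thirds. At AUC 0.5 a separate check gave 0.134 corrected to 0.050 against a true 0: 0.084/0.134 = 63%.

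**The case against.** The strongest reply is that the study's main inference does not use a cut-off. Its aim is to compare markers, which is done on AUCs, and the sample size is also set on the AUC. This stands. A reader might infer that the comparison of lactate with the CO₂-derived parameters is biased, but the documents do not support that. An uninformative marker would also be reported with an AUC near 0.5 beside its inflated J.

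A second reply is that a condensed article may leave validation to a fuller plan. In part this stands: that cut-offs are evaluated in the same patients is inferred from the description of a single cohort. But the threshold rule itself is stated, and following it as written gives biased figures. The Discussion's caveat on external validity concerns the single centre, which is a different matter.

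Third, the bias is modest. At AUC 0.7 with 46/36 it is about 5 points per measure, against a standard deviation of 6 to 7 points for the error in one trial. That is true, but sampling error has no direction and an interval can show it, whereas this bias always favours the marker.

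Two stronger readings are tempting and go beyond the text. Four markers at four sampling times suggest 16 threshold searches, but the article does not say that a threshold will be derived at every time. Nor does it name an interval method for the accuracy measures, so it cannot be faulted for using binomial intervals that ignore the search.

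**Conclusion.** The point holds for the cut-off-based accuracy measures and only for those. For an equal-variance binormal marker with true AUC 0.5 to 0.7, J is overstated on average by about 0.10 to 0.13 if 82 patients are analysed and about 0.09 to 0.12 if all 102 are. This is about 4 to 6 points in each of sensitivity and specificity, reaching nearly 7 for an uninformative marker. At AUC 0.8 the excess in J is about 0.08 to 0.09. A reader might take 0.10 to 0.13 as a fixed property of the plan; it is not, since it depends on the number analysed, the true AUC and the marker's distribution. The direction does not change. This should be corrected, but it does not threaten the primary comparison.

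**What to change.** Add the following to the Statistical Analysis section:

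- In each of at least 1,000 bootstrap samples, re-select the Youden cut-off and apply it to the original data. Take the mean difference between bootstrap and original performance as the optimism, and subtract it from sensitivity and specificity only.
- Derive likelihood ratios and predictive values from the corrected sensitivity and specificity and the observed incidence. Do not subtract mean optimism from the likelihood ratios directly: LR+ is infinite in any resample with specificity 1, and in a check at 46/36 and AUC 0.7 about 2.6% of resamples were of that kind.
- Report bootstrap intervals for the cut-off and for the accuracy measures.
- Label the cut-offs as exploratory pending external validation, since about one-third of the bias remains after correction.

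The cost is a short script outside the planned SPSS and MedCalc analysis, and slightly less favourable reported accuracy. No additional patients or samples are needed. The Trial Status section says recruitment had not begun, so the change can be made before any data are seen.

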### Data Management and Dissemination of Results

Only members of the research team will have access to the research data. All data collected will be kept in a patient file and stored in a locker. At the completion of the study, all case report forms will be collated and archived. All electronic files will be password protected. All patient files (hard copy and electronic) will be handled consistent with the regulations of the hospital regarding the retention and disposal of patient records. No interim analyze is planned. The results of this study will be submitted to an international peer-reviewed journal. The results will also be disseminated via national and international scientific meetings. The datasets obtained from the present study will be available from the corresponding author on reasonable request.

## Discussion

Although CO_2_-derived parameters are increasingly used to identify either low-flow status and/or anaerobic metabolism in shock resuscitation, they are not extensively investigated in cardiac surgery patients. Most studies focused on the predictive value of the PCO_2_ gap (23–26). Some other studies took the Pv-aCO_2_/Ca-vO_2_ into account as well (12, 27, 28). However, Cv-aCO_2_/Ca-vO_2_ was not measured in those studies. Although both considered as a surrogate of the respiratory quotient, it is unclear whether Pv-aCO_2_/Ca-vO_2_ is interchangeable with Cv-aCO_2_/Ca-vO_2_ because the relationship between CO_2_ partial pressure and CO_2_ content is not perfectly linear and is influenced by the degree of metabolic acidosis (42, 43), which is a commonly seen situation after cardiac surgery. Our study will compare these two respiratory quotient surrogates directly, which is an important strength.

There are also limitations of the study. First, this study uses a single-center study design, which limits the external validity of the results. Second, central venous rather than mixed venous blood samples will be taken for the calculation of all the CO_2_-derived parameters. Third, although one important purpose of the study is to compare the performance of the surrogates of the respiratory quotient, no “gold-standard” method will be used for the measurements of the respiratory quotient.

## Trial Status

Protocol version number and date: version 1.0, January 21st, 2020. Recruitment is not started yet, and it is expected to continue until June 2023 to complete patient recruitment.

